### Efficacy analyses

#### Primary endpoint

The full analysis set will be used for the primary endpoint.

The primary endpoint is the change from baseline (inclusion visit) at end of treatment (last visit) in the Clinician ARI total score. An analysis of variance will be performed to study the evolution of Clinician ARI total score (dependent variable) according to the three treatment groups and baseline value of ARI as a covariate. Each experimental group will be compared to the control group.

The treatment effect will be estimated by the least square mean (LSMean) of the difference with its two-sided 95% confidence interval. A graphical display of the LSMean and associated 95% confidence intervals for each treatment will be presented. In the event that marked deviations from the assumption of normality are observed, an additional analysis on the primary efficacy variable will be performed using non-parametric method.

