## Methods

### Assignment of interventions (for controlled trials)

#### Allocation

##### Sequence generation {16a}

The randomization will be done with Ennov-Clinical software (CS-random module). The randomization will be centralized, available online, and stratified by minimization based on centre and on two age classes (6–11 and 12–15 years) and medication status (according to major classes of psychotropic), balanced with a 1:1:1 ratio. Each subject (i.e., here duo or trio of child and parents), who meets the eligibility criteria and signed informed consent, will be randomly assigned to one of the three study groups by the study investigator.

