#### Demographic and baseline characteristics {20c}

To ensure comparability, patient demographic and baseline characteristics (including medical history and prior medications) will be summarized by group using descriptive statistics. For continuous variables, descriptive statistics (*n*, mean, standard deviation, standard error, median, minimum, and maximum) will be provided. For categorical variables, patient counts and percentages will be provided. Categories for missing data will be presented if necessary.

In the case of non-comparability for one or more parameters, an adjustment will be made on this/these parameter(s) for analysis of the judgment criteria. A multivariate linear regression model may be performed to account for potential confounders.

The type of missing data for the variables of interest will be determined. Conditional rejection of the hypothesis NMAR (Not Missing at Random)—the assumption MCAR (Missing Completely at Random) against MAR (Missing at Random)—will be tested by studying the relationship between the variable status (missing or not) and the values of the covariates. If the missing data is type MAR or MCAR, a multiple imputation (Rubin, 1987) will be implemented for a sensitivity analysis. In order not to increase the database and to get a good estimate of the variance parameters, five imputations will be realized.

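### The primary model omits the three minimisation factors, so its test is conservative if they are prognostic, and a separate rule lets chance imbalance choose further covariates

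*Protocol article*

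**What the plan says.** Three places in the protocol article bear on this.

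- **Allocation (Sequence generation {16a}).** Randomisation is "stratified by minimization based on centre and on two age classes (6–11 and 12–15 years) and medication status", the last by major psychotropic class, and "balanced with a 1:1:1 ratio".
- **Primary model (Efficacy analyses, Primary endpoint).** The Clinician ARI total score is analysed "according to the three treatment groups and baseline value of ARI as a covariate". "Each experimental group will be compared to the control group", and "The treatment effect will be estimated by the least square mean (LSMean) of the difference with its two-sided 95% confidence interval". None of the three minimisation factors is named here, and no other section adds them.
- **Further covariates (Demographic and baseline characteristics {20c}).** "In the case of non-comparability for one or more parameters, an adjustment will be made on this/these parameter(s) for analysis of the judgment criteria". The next sentence adds: "A multivariate linear regression model may be performed to account for potential confounders". The section gives no list of variables and no criterion for imbalance. It does not call this adjustment a sensitivity analysis, although it does give multiple imputation that label a few lines later.

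**The concern.** Minimisation makes the arms alike on the chosen factors, so whatever those factors explain of the outcome largely drops out of the difference between arms. A model without the factors still counts that variation as residual noise. It therefore reports a standard error larger than the real one, the 95% intervals cover more than 95%, and the 5% test rejects less than 5% of the time under the null. Precision that the allocation has already secured is not used.

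The rule in {20c} does not make up for this. In a properly randomised trial baseline imbalance is chance, and choosing covariates by imbalance ignores how strongly they predict outcome. Factors balanced by design will seldom look unbalanced, so the rule tends to pass over the very variables that belong in the model. Without a list or a threshold, the covariates of the endpoint analysis are also not settled in advance.

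**Working it through.** **Inputs from the article (Sample size {14}).** Expected changes are −2, −2 and −0.5; difference 1.5; SD 3; 77 per group; two-sided alpha 0.05; power 90%.

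**Input assumed.** R² is the share of residual variance explained by centre, age class and medication status. The article gives no value; 5% to 20% is shown, with 0 as the reference. Balance on the factors is taken as near perfect.

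**1. The plan's own figure.** The mean of the three changes is −1.5, so the variance of means is (0.25 + 0.25 + 1)/3 = 0.5, as stated. The noncentrality is 3 × 77 × 0.5/9 = 12.83, and the one-way ANOVA has power 0.900 at 77 per group (0.896 at 76). The stated 77 reproduces, so the sample size is not at issue here.

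**2. One active arm against TAU under the planned model.** The model SE is 3 × √(2/77) = 0.483 and the interval half-width is 1.96 × 0.483 = 0.95. With pooled df = 3 × 77 − 3 = 228, power is 0.871 at R² = 0.

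**3. Effect of omitting balanced factors.**

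- True SE = model SE × √(1 − R²).
- True type I error = 2Φ(−1.96/√(1 − R²)).
- Planned power: the estimate varies with the smaller true SE but is still judged against the larger model SE.
- Adjusted power: noncentral t with SD 3√(1 − R²) and 228 df, ignoring the degrees of freedom that the extra terms use.

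| R² | True SE / model SE | Type I error, planned | Power, planned | Power, adjusted | Gain (points) |
|---|---|---|---|---|---|
| 0 | 1.000 | 0.050 | 0.871 | 0.871 | 0 |
| 0.05 | 0.975 | 0.044 | 0.877 | 0.887 | 1.0 |
| 0.10 | 0.949 | 0.039 | 0.883 | 0.903 | 2.0 |
| 0.15 | 0.922 | 0.034 | 0.890 | 0.918 | 2.8 |
| 0.20 | 0.894 | 0.028 | 0.896 | 0.932 | 3.6 |

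Planned power rises with R² too, because minimisation improves the true precision whether or not the model uses it. The fair comparison is therefore within each row. Setting every adjusted figure against 0.871 would overstate the gain.

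**4. Simulation check.** Settings: N = 231, biased-coin minimisation with probability 0.8, 3,000 runs per setting; 8 centres and 3 medication classes are assumed.

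- At R² = 0.10, type I error was 0.035 with the planned model and 0.045 with the factors included. At 0.20 the figures were 0.027 and 0.046.
- Under simple randomisation at R² = 0.20, the baseline-only model gave 0.055. The conservatism therefore comes from the mismatch between model and allocation, and not from omitting covariates as such.

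**5. The imbalance rule.** The article sets no trigger, so p < 0.05 was assumed, applied to the three factors and six other baseline variables. It changed the model in about 27% of minimised trials. At R² = 0.20, type I error under this rule was 0.026, against 0.027 for the planned model. The rule neither inflated type I error nor cured the conservatism.

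**The case against.** Several points on the other side stand.

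- **Direction.** A reader might infer from a test that misses its nominal level that false positives are more likely. The calculations show the opposite: type I error at or below 5% and coverage at or above 95%.
- **Size.** It rests on an R² that the article does not give. Both programmes are delivered online by the same instructors and baseline assessment is by video-conference, which suggests a modest centre effect, although case mix and local TAU may still differ. The SD of 3 comes from an ANOVA without covariates, so it is not the residual SD of the baseline-adjusted model.
- **Status of {20c}.** A reader might infer that the primary model will be chosen from an unblinded baseline table. The article does not say so. It refers to a blinded data review and places analysis after approval of the SAP. The imbalance rule appears among baseline characteristics, after a heading for exploratory analyses, and does not expressly replace the primary model. But it says the adjustment will be made for the judgment criteria generally, which leaves its relation to the primary analysis unsettled.
- **Which ARI.** One could call the covariate unspecified, since parent and clinician versions are both collected at baseline. The same sentence names the Clinician ARI as the dependent variable, so the ordinary reading is clear and the point is editorial.
- **The SAP.** It is not shown and may add the factors. However, the article already states a specific model and a mandatory adjustment rule, and a SAP that followed them would carry both forward.

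**Conclusion.** The point holds as one of efficiency and pre-specification. The stated primary model does not match the allocation. If the minimisation factors explain 5% to 20% of residual variance and balance is near perfect, the true type I error is about 0.044 to 0.028 and 1 to 4 points of per-contrast power are given up. Both effects vanish at R² = 0. The mismatch itself is plain from the text; its size is conditional on the assumed R².

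The fault in the {20c} rule is that it leaves the covariates of the endpoint analysis open to chance imbalance and to judgement, and tends to miss the minimised factors. No inflation of type I error was found from it.

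**What to change.** State the primary model as change in CL-ARI on arm, baseline CL-ARI, age class, medication class and centre, with centre as a random effect or with small centres pooled by a rule set in advance. Naming CL-ARI also settles the editorial point on the covariate. Delete the imbalance-triggered adjustment in {20c}, or move it to a labelled sensitivity analysis.

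The cost is wording in the protocol and SAP, since the three factors are already recorded for randomisation. Some degrees of freedom are used; how many depends on the number of centres and medication classes, which the article as shown does not give.

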#### Secondary endpoints

Secondary efficacy endpoints (change at completion of Clinician and Parent ARI, CGI-I score, PAFAS, change in specific CBCL 6–18, FMSS, and personality test scores) will be analyzed using the same methods as the primary endpoints.

### Exploratory analyses {20b}

#### Observance

The number of performed sessions will be described. The discontinuation from the trial due to any cause (or due to specific causes) will be also reported and compared between groups.

Analyses for additional subgroups are not planned in the main study.

#### Demographic and baseline characteristics {20c}

To ensure comparability, patient demographic and baseline characteristics (including medical history and prior medications) will be summarized by group using descriptive statistics. For continuous variables, descriptive statistics (*n*, mean, standard deviation, standard error, median, minimum, and maximum) will be provided. For categorical variables, patient counts and percentages will be provided. Categories for missing data will be presented if necessary.

In the case of non-comparability for one or more parameters, an adjustment will be made on this/these parameter(s) for analysis of the judgment criteria. A multivariate linear regression model may be performed to account for potential confounders.

The type of missing data for the variables of interest will be determined. Conditional rejection of the hypothesis NMAR (Not Missing at Random)—the assumption MCAR (Missing Completely at Random) against MAR (Missing at Random)—will be tested by studying the relationship between the variable status (missing or not) and the values of the covariates. If the missing data is type MAR or MCAR, a multiple imputation (Rubin, 1987) will be implemented for a sensitivity analysis. In order not to increase the database and to get a good estimate of the variance parameters, five imputations will be realized.

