### Statistical methods

#### {20a}

A statistical analysis plan (SAP) will be prepared by the sponsor. Statistical analyses will be performed with SAS® version 9.4 or higher (SAS institute, North Carolina, USA).

Data will be analysed under the responsibility of the Unit of the Clinical research of CHU Montpellier with the SAS® software (SAS Institute, Cary, NC, USA).

The statistical analysis plan (SAP), covering all the analyses to be performed on all data, will be written before database lock.

Population sets

Four analysis, sets will be defined for this study:The Enrolled Set (ES) will include all subjects who sign an Informed Consent form.The Randomized Set (RS) will include all subjects who are randomized.The Full Analysis Set (FAS) will include all subjects who are randomized and have a valid primary efficacy measurement.The Per Protocol Set (PPS) will include all subjects who are in the FAS and who do not have an important protocol deviation that could affect the evaluation of the main outcome.

The FAS will be the primary set used for analyses/summaries of the primary efficacy variable, as well as for all secondary and other efficacy variables; the robustness of the analyses/summaries on the primary and key secondary efficacy variables will be assessed using the PPS.

The ES will be used for summarizing only the relative frequency of screen failures. The ES or RS will be used to establish the flow chart.

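### Multiple imputation, the only stated missing-data sensitivity analysis, depends on a MAR/MCAR classification that observed data cannot establish, and no stated analysis probes NMAR

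*Protocol article*

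**What the plan says.** All of this is in the Protocol article.

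- **Missing-data rule** (Demographic and baseline characteristics {20c}). The type of missingness is to be determined first. The sentence begins "Conditional rejection of the hypothesis NMAR (Not Missing at Random" and goes on to MCAR against MAR, which "will be tested by studying the relationship between the variable status (missing or not) and the values of the covariates". Then: "If the missing data is type MAR or MCAR, a multiple imputation" is to be carried out, as a sensitivity analysis. Nothing is stated for data judged NMAR.
- **Number of imputations** (same section). The reason given is "In order not to increase the database and to get a good estimate of the variance parameters", and on that ground "five imputations will be realized".
- **Analysis sets** ({20a}). "The Full Analysis Set (FAS) will include all subjects who are randomized and have a valid primary efficacy measurement". The FAS is the primary set for efficacy. The other robustness check uses the Per Protocol Set, which is a subset of the FAS. A Randomized Set is also defined, but its only stated use is the flow chart.
- **Expected loss** (Sample size {14}). Dropout of around 15%, with 270 families included.

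**The concern.** MCAR, MAR and NMAR differ in what the probability of being missing depends on. Relating the missingness indicator to observed covariates can reveal a departure from MCAR. Whether missingness also depends on the outcome that was not seen is the question that separates MAR from NMAR, and observed data carry no information on it without further assumptions. A rule that permits imputation only once the data are known to be MAR or MCAR therefore rests on something nobody can know.

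Two things follow. Whether the one missing-data sensitivity analysis is run becomes a judgement made after the data are in, on a basis the plan does not give. And whichever way that judgement goes, NMAR is not examined: if NMAR is suspected, no analysis is stated; if it is not, only an analysis that assumes MAR is stated. The primary analysis is of families with a measured outcome and the Per Protocol Set lies inside it, so neither says anything about the families who are lost.

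**Working it through.** **1. The planned loss.** The sample-size section reproduces. Expected changes of -2, -2 and -0.5 give a variance of means of 0.5. With SD 3 and alpha 0.05, the one-way ANOVA has power 0.9003 at 77 per group (0.896 at 76). Inflating for dropout, 77/0.85 = 90.6, so 91 per group against the stated 90; 1 - 77/90 = 14.4%, which fits a rate of around 15%. The expected number without a primary outcome is 0.15 × 270 = 40.5 families.

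**2. The two readings of the condition.** The sentence on NMAR is hard to parse.

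| Reading | What the covariate test does | Consequence |
|---|---|---|
| NMAR must first be rejected, using the covariates | Asked to do what it cannot | The condition can never properly be met |
| NMAR is set aside, then MCAR is tested against MAR | Has two outcomes, both leading to imputation | The condition does no work; NMAR is excluded by assumption with no basis given |

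On either reading the condition cannot be established from the data, and no stated branch examines NMAR.

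**3. What the covariate test can see.** Simulation with 90 families per arm, about 15% missing, a true effect of -1.50 per active arm against TAU, and 4000 trials per mechanism. Missingness was tested against arm and baseline at the 5% level. The mechanisms are assumptions. In the NMAR case, active-arm families with a poor outcome and TAU families with a good outcome drop out more often, at similar overall rates.

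| Mechanism | Test finds a relation | Complete-case effect | Effect after MAR imputation |
|---|---|---|---|
| MCAR | 4.6% | -1.50 | -1.50 |
| MAR (depends on baseline) | 92.7% | -1.51 | -1.51 |
| NMAR | 5.4% | -2.12 | -2.12 |

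The test separates MAR from MCAR but not NMAR from MCAR. It is also silent in the one case with bias: -2.12 - (-1.50) = -0.62 points. The imputation here used only arm and baseline, as the point estimate for unlimited imputations, so it matches complete cases. Adding the 1-month CL-ARI might recover part of the bias, but MAR imputation does not address NMAR as such.

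**4. Five imputations.** The fraction of missing information (FMI) is not in the documents. I take 0.15, the dropout rate, with a range of 0.05 to 0.30.

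- Relative efficiency, 1/(1 + FMI/m): at m = 5, 1/(1 + 0.15/5) = 0.971 (range 0.990 to 0.943); at m = 50, 0.997.
- Coefficient of variation (CV) of the between-imputation variance, √(2/(m-1)): at m = 5, √(2/4) = 71% on 4 degrees of freedom; at m = 50, √(2/49) = 20%. On 4 degrees of freedom the 95% range runs from 0.36 to 8.3 times the estimate.
- CV of the total variance, approximately FMI × the figure above: at m = 5, 0.15 × 0.71 = 11% (range 4% to 21%); at m = 50, 3%.
- Monte Carlo error of the imputed contrast, √(B/m) with B = FMI × SE²/(1 + 1/m) and SE = 3√(2/77) = 0.483: at m = 5, B = 0.15 × 0.2338/1.2 = 0.0292 and √(0.0292/5) = 0.076 points, 16% of the SE; at m = 50, 0.026 points, 5% of the SE.

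**The case against.** The strongest defence is the second reading in the working. If NMAR is merely set aside, both outcomes of the test lead to imputation and it would in effect always run. That is a fair reading, so the text does not prove that the analysis would be skipped. It does not rescue the rule, because the wording still makes imputation depend on data being MAR or MCAR and gives no means of knowing that.

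A second defence is that a tipping-point analysis is commonly left to the SAP, which is to be written before database lock. That is so, and its absence alone would not be a finding. The fault is the condition that the article itself fixes. The NMAR analysis belongs to the remedy because deleting the condition alone would leave only MAR-based analyses.

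Stronger readings are tempting, and the documents do not support them:

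- **That protection is lost exactly when it is needed.** MAR imputation would not repair NMAR bias; the simulation gives -2.12 with or without it.
- **That imputation is confined to the FAS and so changes nothing.** The FAS holds only families who are "randomized and have a valid primary efficacy measurement", but {20c} does not say which set is imputed.
- **That the trial result could turn on the random seed.** The primary analysis under Efficacy analyses uses no imputation.
- **That informative dropout is the main threat.** The documents give a rate and no evidence of informative loss. They also ask for a final visit after withdrawal ({18b}) and compare discontinuation between groups ({20b}).

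**Conclusion.** Wrong as written. The MAR/MCAR condition cannot be established from observed data on either reading, and the stated plan contains no analysis of departures from MAR, while about 15% of families (some 40 of 270) are expected to have no primary outcome. The conclusion about the condition rests on logic and not on the simulation. The 0.62-point bias illustrates one deliberately adverse, assumed mechanism and is not a forecast for this trial.

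The number of imputations is a side point. The stated reason, a good variance estimate, is not supported when the between-imputation variance has 4 degrees of freedom and a CV of about 71%. The practical loss is small: about 3% in efficiency at an assumed FMI of 0.15, and less if baseline and 1-month scores predict the outcome well. All of this concerns the sensitivity analysis and leaves the primary estimate untouched.

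**What to change.** In {20c}, and in the SAP:

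1. Delete the MCAR/MAR/NMAR test and the condition that depends on it. Describing missingness by arm and baseline characteristics can stay as description.
2. State that multiple imputation will always be run on the Randomized Set, with an imputation model containing arm, baseline and 1-month CL-ARI, and the minimisation factors (centre, age class, medication status).
3. Add one pre-specified NMAR analysis: either delta-adjusted imputation taken to a tipping point, or reference-based imputation in which active-arm families without an outcome are imputed from TAU. Fix the choice and the range of deltas before database lock.
4. Replace five imputations with a larger number, for example 50, and drop the stated rationale.

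The cost is a few sentences and a little more programming. The 1-month CL-ARI and the minimisation factors are already collected, so no new data are needed, and the SAP has still to be finalised under the article's own timetable.

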### METHODS: Oversight and monitoring {21a}

Data monitoring will be carried out by an independent safety monitor who will ensure the compliance with the trial regulatory aspects. Additionally, they will verify data collection. The safety monitor acts as a representative of the study promotor.

Site training and monitoring procedures

The monitor must present the protocol and all procedures related to the study during an initial visit before the first patient is included. A CRF of completion guidelines will be provided to the Investigator.

Direct access to source data/original documents

The monitor will be allowed to have access to all source documents needed to verify the entries on the e-CRF and other protocol-related documents.

Accuracy and Reliability of Data

To ensure accurate, complete, and reliable data, the sponsor (or their representatives) will do the following:Provide instructional material to the study sites, as appropriate.Provide a start-up training session to instruct the investigator(s) and study coordinator(s). This session will provide instruction on the protocol, the prompt, and full completion of the clinical report forms, study procedures, and the transmission of data in a timely manner to the clinical database for statistical analyses.Make periodic visits to the study site.Be available for consultation and stay in contact with the study site personnel by mail, telephone, and/or fax.Review and evaluate Case Report Form data and use.Conduct quality review of database.

